## Abstract

**Background:**

One in 5 young people grow up in a family where one parent has experienced a mental health problem or substance use concern. Compared with their same-aged peers, these youth are at a higher risk of academic failure and acquiring a substance abuse and/or mental health issue. There is a paucity of accessible, age-appropriate interventions that address their needs.

**Objective:**

A 6-week, web-based intervention, “mental illness: supported, preventative, online, targeted” (mi.spot), was developed based on previous research and the competence enhancement model. This paper describes the protocol for a randomized controlled trial and details how the usage, safety, acceptability, and feasibility of the intervention will be determined.

**Methods:**

Participants will be recruited through social media and clinician referral. A total of 70 Australians, aged 18 to 25 years, who grew up with parents with a mental illness or substance use concern will participate in a 2-arm parallel randomized controlled trial. The assessment will consist of a baseline measurement and 2 follow-up periods, posttest and 6-week follow-up, using the Mental Health Continuum short form; the Depression, Anxiety, and Stress Scale; the Coping Orientation to Problems Experienced inventory; the General Help Seeking Questionnaire; the Social Connectedness Scale; the Mental Health Literacy Scale; the General Self-Efficacy Scale; and the Attribution of Responsibility for Parental Mental Illness Measure. Impact will be examined at pre, post, and follow-up time periods using analyses of variance that will include a within-subjects factor (time) and a between-subjects factor (intervention/control). Facilitator interviews will ascertain intervention feasibility. Participant interviews will ascertain intervention acceptability. Interview data will be analyzed within a qualitative framework. Usage (data analytics) across site features and several indicators of clinical safety will also be reported.

**Results:**

The impact of mi.spot will be examined at pre, post, and follow-up time periods using analyses of variance on each of the measures outlined above. There will be a within-subjects factor (time) and a between-subjects factor (intervention/control). Data analysis will employ the intention-to-treat principle by including all participants in the analyses. Qualitative interview data will be analyzed using interpretative phenomenological analysis along with respondent validation. The Monash University Human Research Ethics Committee (reference number: 2019-18660-30434) approved the trial on April 17, 2019. As of October 2, 2019, 30 participants were enrolled in the control group and 34 participants were enrolled in the intervention group. Result are expected to be submitted for publication in December 2020.

**Conclusions:**

Study results will provide reliable evidence on a web-based intervention that has the potential to make a difference to the lives of many vulnerable young adults. Implementation guidelines are needed to embed the intervention in different service sectors.

**Trial Registration:**

Australian New Zealand Clinical Trials Registry ACTRN12619000335190; https://anzctr.org.au/Trial/Registration/TrialReview.aspx?ACTRN=12619000335190

**International Registered Report Identifier (IRRID):**

DERR1-10.2196/15626

## Introduction

### Background

A systematic review recently substantiated that up to 45% of clients in adult mental health services are parents with children [1]. Maybery et al [2] estimated that more than 1 in 5 children have 1 parent with a mental health problem. Compared with their same-aged peers, these children are at high risk of school dropout and failure [3], being taken into care [4], and acquiring a substance misuse concern and/or mental illness [5]. Their problems often continue into adulthood; a 30-year follow-up found that the risk of major depression was approximately three times as high in the children whose parents had depression, with the period of highest risk for first onset between 15 and 25 years of age [6]. Given the prevalence and needs of this at-risk group of young people, it is imperative that there are evidence-based, easily accessible interventions targeted at their specific needs.

One of the traditional ways of supporting young people in these families has been through face-to-face peer support groups [7]. These aim to prevent the onset of mental health problems in young people by providing social support, psychoeducation, and training in adaptive coping [7]. In a randomized controlled trial based in the Netherlands, van Santvoort et al [8] showed that children in such an intervention experienced a greater decrease in negative cognitions and sought more social support compared with the control group. Notwithstanding these benefits, face to face programs have several recruitment issues related to stigma, referral pathways, transport, and time [9]. There are also relatively fewer programs for young people living in rural and remote areas compared with their urban counterparts [10]. In addition, face-to-face peer support programs target children aged 12 to 18 years and not older youth aged 18 to 25 years [7].

### Web-Based Interventions

Web-based interventions have the potential to circumvent stigma, reach, and access issues. Furthermore, young adults are increasingly turning to the internet to search for health information and to share personal information [11,12] because it is highly engaging, accessible, anonymous, and often free of charge [13]. Young adults living in these families have indicated a preference for online support [14] with specific preferences for topics on psychoeducation, managing the parent-child relationship, and strategies to build resilience and improve coping and mental health [15]. There are some online interventions for youth aged 18 to 25 years whose parents have a mental illness/substance use concern, although none are in English and are still in the early stages of development [16-18]. For example, a randomized controlled trial in the Netherlands, of an online intervention called Kopstoring, found positive trends toward a reduction in internalizing symptoms but no significant differences in self-reported depressive symptoms and internalizing problems [18]. Further work is needed to consolidate and substantiate the evidence base in this area and ensure that interventions designed for this group are effective.

### Objectives

This paper describes the protocol for a randomized controlled trial for the mental illness; supportive, preventative, online, targeted (mi.spot) intervention. It is hypothesized that following the mi.spot intervention, young adults will report the following:

Significant improvements in mental health and well-being (primary outcomes)Significant improvements in coping, social connectedness, and attribution of responsibility for parental mental illness (secondary outcomes)Significant increases in help seeking and mental health literacy (secondary outcomes).

Furthermore, the study will determine what components of the site participants use and do not use, along with their views about intervention safety and acceptability. Facilitators’ views of the feasibility of the intervention will also be sought.

## Methods

### Design

This 2-arm parallel randomized controlled trial will compare outcomes at posttest and 6-week follow-up for mi.spot and control participants. The protocol is in accordance with the Consolidated Standards of Reporting Trials of Electronic and Mobile HEalth Applications and onLine TeleHealth checklist. The study was undertaken in 2019. The protocol was registered by the Australian and New Zealand Clinical Trials Register on May 5, 2019. The registration number is ACTRN12619000335190.

### Ethics

For inclusion, all participants must give implied consent online before completing the questionnaires. Written consent is required for the interviews. Ethics approval for this study was obtained from the Monash University Human Research Ethics Committee (reference number: 2019-18660-30434) on April 17, 2019.

### The Intervention

mi.spot is a 6-week professionally moderated online intervention for emerging adults (aged 18-25 years inclusive) who have a parent with a mental illness or substance use concern (Figure 1). It is based on the competence enhancement model, which incorporates cognitive behavioral principles and a strengths-based approach [19]. A reference group was formed to guide intervention development, consisting of expert clinicians, researchers, and young adults with lived experience. Drawing on the known risk and resilience factors for this particular group of young adults [20], the intervention aims to improve psychoeducation; increase adaptive coping, connectedness, and knowledge about healthy relationships; encourage help-seeking behaviors; decrease feelings of attribution about their parent’s illness; and foster well-being and mental health (refer to the paper by Reupert et al [21] for further details regarding the theoretical background and empirical rationale for the intervention).

The site is anonymous, and participants give themselves a nickname they use in all online interactions. All features are optional, and participants may choose to *lurk* rather than actively contribute. The approach includes 6 professionally facilitated online weekly chats that run for 1 hour a week on set topics with accompanying video, audio, and print resources (Table 1). The accompanying resources are made available when the accompanying session is offered. There are also opportunities for private one-to-one online counseling sessions between the participant and the facilitator, which can be initiated by either the participant or by one of the facilitators if they believe the participant requires additional support.

The site includes mi.thoughts.spot, which functions as an asynchronous, online private diary for participants to use and which is visible only to the individual participant and facilitator. mi.thoughts.spot allows participants to record their feelings, practice reframing automatic negative thoughts and challenge unhelpful beliefs using a cognitive behavioral approach. There are also opportunities for participants to chat with each other on group threads. The facilitator’s role is to monitor the site, encourage young adults to apply a strength-based cognitive behavioral model, facilitate weekly topics, and promote healthy peer sharing and support.

**Figure 1 figure1:**
[figure not shown]
Screenshot of the mental illness; supportive, preventative, online, targeted intervention.

**Table 1 table1:** The weekly mental illness; supportive, preventative, online, targeted topics.

Topic	Description
What is mi.spot all about?	This session introduces the site and provides participants with an opportunity to get to know each other and the facilitators. Guidelines (rules) for using the site are described, and the various components of the site are described. The cognitive behavioral approach is explained and practiced.
Learning more about mental health and illness	This session delivers basic psychoeducation about different types of mental illnesses. Participants are invited to reflect on what they know about their parent’s illness or substance use issue, what they want to know, and how their parents’ illness might impact their mental health and well-being. Specific genetic vulnerabilities are discussed. Ways to promote well-being are emphasized.
Me, my parent, and other relationships	In this session, participants reflect on their relationship with their parent(s) and consider how these relationships might inform other intimate relationships. Strategies for forming healthy relationships and boundary setting are also shared.
Managing stress	In this session, participants identify a current stressor and consider what they did or might do to manage this. They are prompted to share adaptive coping strategies and useful ways to regulate emotions.
Caring—who me?	Participants are invited to describe any caring responsibilities they may have and the potential positive and negative impacts that caring for others might have. The principles of self-care and self-compassion are also covered.
Taking control of my life	In the final week, participants consider what they have learnt over the 6 weeks. This session also covers help-seeking strategies, including an emphasis on asking for help early, who they might turn to, and how they might ask for help. A list of relevant services is shared.

### Setting and Intervention Facilitators

The intervention will be delivered from the Krongold Clinic at Monash University, a university-based teaching and research clinic in Australia. Masters’ level psychology students will deliver the intervention under the supervision of qualified and experienced psychologists. Conduct of the trial will be led by the principal investigator and supported by a research team, all of whom will receive training in the requirements of the study protocol. Before training, all students were required to have successfully completed a 2-day workshop on assessing and responding to suicide and self-harm.

Experienced practitioners will deliver training specific to mi.spot over 2 days. The first day will focus on generic online counseling skills (in both group and individual counseling mode) and the second day will specifically examine the mi.spot intervention and how it should be delivered using simulated online sessions. Face-to-face training will be undertaken 2 weeks before starting the intervention. Fidelity checks for the 6 weekly sessions are built into the program at the facilitator level to ensure that all topics are covered. All features of the intervention are manualized, with guidelines provided for each function of the website.

### Safety

The safety protocol for the intervention consists of guidelines around privacy, online safety, and clinical safety. During the initial telephone call, during week 1, and as outlined under the online tab *things you need to know*, participants will be informed of and required to accept the terms of use for protecting their privacy and prohibited behaviors (ie, disrespectful, racist, or offensive comments or statements glorifying suicide or self-harm). The site will be checked, at a minimum twice a day, to ensure that there have been no rule violations (bullying, glorification of substance use, or self-harm). Participants will be informed that failure to comply may result in temporary or permanent withdrawal from the intervention.

In addition, every week, participants will be invited, via the site, to report any feelings of distress. If identified as being in distress, participants will be invited to an online one-to-one counseling session, with referrals provided if required. If a participant discloses statements indicating high distress (eg, suicidal ideation), the facilitator will conduct a telephone risk assessment and, where necessary, undertake 1 or more of the following procedures: (1) inform the supervisor, (2) inform the participant’s nominated emergency contact, and/or (3) liaise with suitable emergency services. Safety procedures are clearly outlined in the manual for facilitators to follow for any adverse event. Moreover, the 24/7 emergency numbers are visible under the tab *crisis contacts*.

Safety will be recorded in terms of the number of inappropriate posts (eg, bullying, the glorification of substance use, and self-harm), the tracking of participants’ mood over the 6 weeks, and participants’ retrospective reports of feeling safe/unsafe during interviews post the intervention.

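### After a high-distress disclosure, the stated safety rule requires only a telephone risk assessment; informing the supervisor should be a fixed step too

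*Protocol article*

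**What the plan says.** The Safety section describes two levels of response. Participants are asked regularly about their state: "every week, participants will be invited, via the site, to report any feelings of distress". Those identified as distressed are invited to one-to-one online counseling, with referral if required.

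For statements indicating high distress, such as suicidal ideation, the section first sets a firm step: "the facilitator will conduct a telephone risk assessment". It then says that the facilitator will "where necessary, undertake 1 or more of the following procedures: (1) inform the supervisor, (2) inform the participant’s nominated emergency contact", with contact to emergency services as the third item in the list. It adds: "Safety procedures are clearly outlined in the manual for facilitators to follow for any adverse event". That manual is not available here.

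The section on Setting and Intervention Facilitators says who makes these decisions: "Masters’ level psychology students will deliver the intervention under the supervision of qualified and experienced psychologists". On their preparation it says that "all students were required to have successfully completed a 2-day workshop on assessing and responding to suicide and self-harm".

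The Intervention section describes two private channels. One is the online diary, "which is visible only to the individual participant and facilitator". The other is "opportunities for private one-to-one online counseling sessions between the participant and the facilitator".

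**The concern.** Supervision of trainees exists so that a qualified psychologist can check their judgment. The Safety section makes the supervisor's involvement depend on that same judgment. If a student underestimates the risk during the telephone assessment, nothing in the stated rule brings in a second opinion, and that is the case in which one is most useful.

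Such disclosures are foreseeable. Under Recruitment and Screening, the reference committee chose not to exclude people for mental illness, because mental health conditions are common among young adults from these families. The Safety section itself anticipates suicidal ideation. At stake is participant safety; randomization, outcome measurement and the analysis are not affected.

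**Working it through.** No calculation applies to the core of the point, and there is no figure in the plan to reproduce. The check is a reading of the rule against the rest of the article.

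**Step 1. Which steps are unconditional?**

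| Step after a high-distress disclosure | Status in the Safety section |
|---|---|
| Telephone risk assessment | Required |
| Inform the supervisor | Conditional on need; one of three options |
| Inform the emergency contact | Conditional on need; one of three options |
| Liaise with emergency services | Conditional on need; one of three options |

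**Step 2. Can the rule be followed without the supervisor being told?** Yes, in two ways. First, the facilitator completes the assessment and concludes that nothing further is needed. Second, the facilitator concludes that action is needed and takes only one of the other two options, which satisfies the requirement of at least one. The options may also be combined, so the rule permits notification in every case; it does not require it.

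**Step 3. Does another section make notification mandatory?** No. The safeguards that the article describes are these:

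- Supervision by qualified psychologists (Setting and Intervention Facilitators). This is the most relevant one. It is stated in general terms, without saying when a disclosure must be reported.
- The 2-day suicide and self-harm workshop and 2 days of training specific to the intervention (same section). These improve the trainee's judgment but do not add a second one.
- The entry telephone call, with a self-reported distress rating, a verified telephone number, confirmed emergency contact details and referral elsewhere if in distress or crisis (Study Population; Recruitment and Screening). This acts before delivery starts.
- Site checks at least twice a day, weekly invitations to report distress, counseling with referral, and 24/7 emergency numbers (Safety). These detect distress or direct participants to help.

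Apart from supervision itself, none of these, as described, brings a disclosure to a psychologist.

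**Step 4. Where does the wording matter most?** In the diary and the one-to-one sessions. For a disclosure made there, the only route to the supervisor that the article describes is the facilitator's own report. The article does not describe supervisor access to the site or session records, and it does not rule them out.

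**Step 5. Who could still benefit from a change?** The Abstract reports 34 intervention and 30 control participants enrolled by October 2, 2019: 34 + 30 = 64 of the planned 70, leaving 70 − 64 = 6. The Design section says that the study was undertaken in 2019. Under Allocation/Randomization, control participants are offered the intervention about 12 weeks after randomization. The article gives no dates for the delivery of either round. Those who could still be reached might include wait-list participants, intervention participants still in the program on that date, and people not yet enrolled. How many of them remain cannot be worked out from the article.

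**The case against.** The strongest reply is that a journal article condenses the clinical procedure and names where the detail sits. The manual may say when each step is necessary and may already require that the supervisor be told. The list could also be meant as stepped escalation, from supervisor to emergency contact to emergency services. Standing supervision may bring every such disclosure to a psychologist as a matter of routine. On this view, the point rests on one summary sentence.

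Much of this stands, and it limits the point to the rule as stated. It does not remove the point, because the article is not merely silent: it sets out a rule in which notification is optional. If the manual is stricter, the published wording understates the procedure and should be corrected. If the manual says the same as the article, both need the change.

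A reader might draw three stronger conclusions, none of which the article supports:

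- *That disclosures bypassed supervision in practice.* Nothing in the article shows this.
- *That the rule contradicts the supervision arrangement, or that students act on unguided discretion.* A general statement of supervision is compatible with a conditional reporting rule, and the manual may supply the criteria.
- *That at most 35 participants could benefit, being the wait-list half of 70 (70 / 2).* This is not a true upper limit. It leaves out intervention participants still in the program, or not yet enrolled, on October 2, 2019.

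**Conclusion.** The point holds as a modest, inexpensive safety improvement. As worded, the rule makes only the telephone risk assessment mandatory after a high-distress disclosure. Informing the supervisor is conditional and one of three options, although those applying the rule are trainees. No other section makes notification mandatory.

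The conclusion rests on the published wording alone, and it assumes only that the article states the rule as intended. Neither frequency nor consequence can be given a number, because the article reports no disclosure rate and no facilitator caseloads. Confidence is moderate, because supervision practice and the manual could already close the gap. The change is still worth making: the event is foreseeable and potentially grave, and the supervisors are already in place.

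**What to change.** Reword the Safety section along these lines: after every disclosure indicating high distress, the facilitator conducts a telephone risk assessment and informs the supervisor, whatever the assessment concludes; where needed, the facilitator also informs the emergency contact, liaises with emergency services, or does both. Add that an emergency call must not wait until the supervisor has been reached.

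Check the facilitator manual and make it say the same for any remaining delivery, including to wait-list participants, and for later use of the program. If the manual already requires notification, only the article's wording needs correcting.

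The cost is one sentence, a check of the manual and a small amount of extra supervisor time. No new staff are needed, and randomization, outcomes and analysis are untouched. Participants who have already completed the program gain nothing from the change.

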### Primary Outcome Measures

The primary outcome measures used in this study are as follows:

The Mental Health Continuum short form is an internationally applied and thoroughly validated self-administered rating scale that contains items that measure 3 aspects of well-being: emotional, social, and psychological. Participants are asked the degree to which they have experienced emotional, social, and psychological well-being over the past month. The form includes a 6-point Likert scale from 0=never to 5 every day. Scores on this scale can range from 0 to 70, and higher scores indicate higher levels of well-being [23].The *Depression, Anxiety, and Stress Scale* is an internationally applied and thoroughly validated self-administered rating scale that measures levels of depression, anxiety, and stress. Participants are asked the degree to which they have experienced depression, anxiety, and stress over the past month. A 4-point Likert scale is used from 0 (did not apply to me at all) to 3 (applied to me very much or most of the time) within each of the 3 domains. Normal scores for depression, anxiety, and stress ranged from 0 to 4, 0 to 3, and 0 to 7, respectively, and scores above these ranges indicate mild to extremely severe levels in each domain [24,25].

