### Interviews: Determining Feasibility, Acceptability, and Safety

Individual interviews will be conducted with available (n=8) facilitators 1 to 2 weeks post the intervention to obtain their feedback on the training and the intervention in terms of feasibility, ease of use, practicality, and responsiveness. Individual interviews will also be conducted with 8 to 10 consenting mi.spot participants. Interview schedules for participants will be organized around safety as well as intervention acceptability, defined by the perceived benefit of the intervention and participants’ self-reported confidence in change [33]. If applicable, participants will be asked for their reasons for poor engagement or dropout.

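### The listed safety measures come only from the mi.spot arm; they leave out the trial's own risk assessments and escalations and any count by arm of participants whose DASS scores worsen

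*Protocol article*

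**What the plan says.** The Objective in the abstract promises that the article sets out how safety, among other things, will be determined. The Safety section then names the record. It opens with "Safety will be recorded in terms of the number of inappropriate posts" and continues with "the tracking of participants’ mood over the 6 weeks, and participants’ retrospective reports of feeling safe/unsafe during interviews post the intervention". The abstract's Methods refer only to several indicators of clinical safety and name none.

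The same section describes what happens when a participant is in trouble. On the site, "every week, participants will be invited, via the site, to report any feelings of distress". If a disclosure indicates high distress, "the facilitator will conduct a telephone risk assessment and, where necessary, undertake 1 or more of the following procedures", and these procedures run up to the emergency contact and the emergency services. It adds that "Safety procedures are clearly outlined in the manual for facilitators to follow for any adverse event".

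Three other sections bear on the point:
- **Interviews:** "Individual interviews will also be conducted with 8 to 10 consenting mi.spot participants".
- **Usage:** one-to-one sessions are counted, whether started by the facilitator or the participant, but as a usage figure.
- **Primary Outcome Measures, Assessments and Data Analysis:** the DASS is a primary outcome, completed by both arms at baseline, posttest and follow-up, and analysed by time and arm.

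**The concern.** The most serious events that the protocol foresees are described as procedures and are not listed as outcomes. A report that kept to the list could show few inappropriate posts and reassuring interviews and say nothing of participants who needed a risk assessment or the emergency services.

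The listed measures also have no comparator. Mood over six weeks in one arm cannot be separated from ordinary fluctuation, and this population is not screened out for mental illness. The trial does hold a randomised comparison of distress, but the plan uses it only for mean change. If most mi.spot participants improve a little and a few worsen, the mean can still favour mi.spot.

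**Working it through.** The plan states no figure for safety, so there is none to reproduce. The check sets the sections side by side and then sizes the proposed comparison.

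**1. Where each listed measure arises**
- *Inappropriate posts:* made on the site. Controls are offered the intervention only after the intervention group's postintervention questionnaires (Allocation/Randomization).
- *Mood over 6 weeks:* the article does not say how mood is tracked. The weekly distress report it describes is made through the site.
- *Safe/unsafe reports:* from interviews with mi.spot participants only.

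None of the three yields a control-arm value at posttest.

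**2. What is described but not listed**
- Telephone risk assessment, notice to the supervisor or emergency contact, and emergency-service liaison: in Safety, as procedures.
- One-to-one sessions: counted, under Usage.
- DASS in both arms: analysed as a primary outcome, with no count of participants who deteriorate.

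**3. Why a mean can hide a minority.** As an illustration with assumed values, let 15% of an arm worsen by 0.5 SD and 85% improve by 0.2 SD. The mean change is 0.85 × 0.2 − 0.15 × 0.5 = 0.170 − 0.075 = 0.095 SD in the direction of improvement. About one participant in seven has worsened, yet the arm mean has improved.

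**4. Precision of a count by arm.** Inputs are 70 recruited, so 35 per arm if equal, and dropout of up to 40% (Participant Numbers), so 35 × 0.6 = 21 per arm. The 15% deterioration rate in each arm is an assumption, because the article gives none. The 95% half-width for a risk difference is 1.96 × √(2 × 0.15 × 0.85 / n):
- n = 35: 1.96 × √(0.255/35) = 0.167, about ±17 points.
- n = 21: 1.96 × √(0.255/21) = 0.216, about ±22 points.

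Power to detect 10% against 30% deteriorating (also assumed) is 55% at 35 per arm and 36% at 21. The table therefore describes and does not test.

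**5. What an arm-wide escalation count offers.** It covers every mi.spot participant. If none of 35 had an escalation, the one-sided 95% upper limit would be 1 − 0.05^(1/35) = 8.2%.

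**6. Which time point is firmer.** Controls are offered mi.spot about 12 weeks after randomisation, while their last questionnaire is put at 13 to 14 weeks (Recruitment and Screening). Some may have access by follow-up, so the posttest comparison is the cleaner one.

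**The case against.** The other side has a good deal to say.

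- **Distress is compared between arms.** The DASS is a primary outcome, so a mean worsening on mi.spot would appear in the main analysis. This stands. A reader might infer that the trial cannot answer its safety question or that harm would go unseen, and the documents do not support that. The gap is confined to individual deterioration.
- **Harm is watched for as it happens.** The site is checked at least twice a day, distress reports are invited weekly, and a facilitator manual covers adverse events. This also stands. The point concerns recording and reporting, not the care given.
- **The article is a condensed account.** The manual or full protocol may hold an event log, and the Safety section does not say that its list is exhaustive. This stands in part. However, the article undertakes to say how safety will be determined and names specific measures, and the escalations are not among them.
- **The interviews are not meant to estimate a rate.** It is tempting to note that no unsafe report among 8 to 10 interviewees leaves a one-sided 95% upper limit of 31% to 26%. The arithmetic is right, but the interviews are analysed qualitatively and the Objectives ask for participants' views. The protocol claims no harm rate from them, so this is not a fault in the plan. Nor are leavers excluded, since interviewees may be asked why they dropped out.
- **The comparison is imprecise, and the escalation count is itself single-arm.** Both are true. They limit what the additions can show, but they do not justify leaving the events out of the report.

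**Conclusion.** The point holds in a limited form. The named safety measures arise only in the mi.spot arm, omit the risk assessments and escalations that the same section describes, and make no use of the DASS to count participants who deteriorate. A report following the list could reassure while such events occurred. A mean worsening would still be seen in the primary analysis, and active monitoring is in place. The point is therefore a cheap improvement to what is reported and does not undermine the trial.

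The gain is modest: about ±17 points on the difference in deterioration at 35 per arm and ±22 at 21. This rests on an assumed 15% rate, equal arms and the protocol's own dropout ceiling. The escalation count assumes that facilitators keep records of these events.

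**What to change.** Add two items to the safety outcomes in the Safety section.

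(a) The number of mi.spot participants with any telephone risk assessment, and with each type of escalation, taken from facilitator records. Report the one-to-one sessions already counted under Usage beside it.

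(b) By randomised arm, at posttest and follow-up, the number and percentage whose score on each DASS domain worsens by a pre-set amount, with the denominator, a risk difference and a 95% CI, labelled descriptive. Fix the amount before data are seen by arm. It should apply at any baseline level. The normal ranges alone will not do: "scores above these ranges indicate mild to extremely severe levels in each domain", so a count of moves out of the normal range would miss everyone already above it at baseline, in a group where mental health conditions are common.

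Also state that the interviews illustrate participants' views of safety and do not estimate a harm rate.

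The cost is a few lines of text, a tally and one table. No new data collection is needed, which matters because 64 of 70 participants were already enrolled by October 2, 2019. No care procedure changes. The drawback is the wide interval, which should be stated with the table.
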